## Method

### Design

The current study will employ a parallel-group, exploratory randomized controlled trial design. The study will follow the CONSORT statement [29], CONSORT E-Health guidelines [30] and the SPIRIT guidelines (Standard Protocol Items: Recommendations for Interventional Trials) [31]. Participants will be randomly assigned to (a) the internet-based Unified Protocol (iUP), or (b) enhanced waiting list control (eWLC). Randomization will follow a 2:1 allocation ratio, with sample size calculations suggesting a required sample of 120 (iUP=80; eWLC=40). Assessments will take place at baseline, 4 weeks, 8 weeks and 12 weeks from baseline. For ethical reasons, the eWLC group participants will be offered iUP treatment after 12 weeks. iUP group participants will be followed up at 16 weeks, 20 weeks and 24 weeks from baseline, so that we can examine (short-term) stability of any effects achieved.

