### Sample size

Sample size was determined in relation to the planned analysis of primary outcomes (i.e. linear mixed models of anxiety/depression severity) and calculated in the R package ‘powerlmm’ [34]. Model parameters (random intercept/slope, residual variance) required for this calculation were estimated from similar data from a previous trial on a transdiagnostic intervention in primary care [26]. Given a 2:1 randomization ratio, longitudinal data collected at four timepoints across both groups, 30% research attrition at the primary endpoint and a moderate post-treatment between-group effect size of *d*=0.5 in line with previous research [21, 35], a sample size of 120 (iUP=80, WLC=40) was estimated to yield sufficient statistical power of 0.83 (a Bonferroni-adjusted *p* value of 0.025 to account for two primary outcome measure would reduce power to 0.75; at a lower attrition rate of 20% rather than 30%, power of 0.80 would be reached even with the Bonferroni-adjusted *p* value).

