### Data analysis

All the analyses will follow the intention-to-treat principle and reporting of the results will adhere to CONSORT recommendations. Missing data analysis will explore missing data patterns and mechanisms. Multiple imputation will be considered where deemed necessary. Linear mixed models will be used to evaluate primary and secondary outcomes. In these models, intercepts and/or slopes will be allowed to vary on the level of the individual where appropriate and time and treatment group as well as their interaction will be included as fixed effects. To allow for the nesting and comparing of models in terms of model fit, models will be estimated via maximum likelihood estimation during model building. Final models will utilize restricted maximum likelihood estimation. Separate linear mixed models utilizing only data from the iUP group will be built to assess the maintenance of effects into follow-up, including random intercepts/slopes and time as a fixed effect. Between-group Cohen’s *d* effect sizes will be calculated based on raw standard deviations [52]. The qualitative data will be analysed using a descriptive-interpretive approach [53].

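### The primary mixed model leaves the baseline group difference free, so its test is valid but less precise than one with a common baseline mean

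*Protocol article*

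**What the plan says.** The Data analysis section applies linear mixed models to the primary and secondary outcomes. On the fixed effects it states that "time and treatment group as well as their interaction will be included as fixed effects". On the random effects it states that "intercepts and/or slopes will be allowed to vary on the level of the individual where appropriate".

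Baseline belongs to the modelled outcome series. The Design section says: "Assessments will take place at baseline, 4 weeks, 8 weeks and 12 weeks from baseline". The Sample size section counts the same four visits: "longitudinal data collected at four timepoints across both groups, 30% research attrition at the primary endpoint".

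That section ties the calculation to the mixed model ("Sample size was determined in relation to the planned analysis of primary outcomes") and assumes "a moderate post-treatment between-group effect size of *d*=0.5 in line with previous research". It reports power of 0.83 for 120 participants (80 and 40). Power falls to 0.75 at a Bonferroni level of 0.025, and 0.80 is reached at that level only if attrition is 20% instead of 30%.

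The article nowhere sets a common baseline mean for the two arms or enters the baseline score as a covariate. It also does not say whether time is linear or categorical.

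**The concern.** When baseline is an outcome and treatment group has its own fixed effect, the model estimates a separate baseline mean for each arm. The interaction with time then measures how differently the arms change from those two baselines. Participants are randomised individually after the initial assessment, so the true baseline means are equal, and the free contrast estimates something already known to be zero in expectation.

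The observed baselines will still differ by chance. With 80 and 40 participants, the standard deviation of that difference is √(1/80 + 1/40) = 0.19 SD. A gap of at least 0.2 SD therefore arises in about 30% of trials, against a target effect of 0.5. A change comparison subtracts the whole gap, whereas a common baseline mean subtracts only the part that predicts the later score.

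What is at stake is precision. The article itself reports 0.75 power once both primary outcomes are controlled, so even a modest gain is useful.

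**Working it through.** **Inputs from the article.** 80 v 40 participants; weeks 0, 4, 8 and 12; d = 0.5 at week 12; attrition 30% (alternative 20%); alpha 0.05 and 0.025.

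**Assumptions.** The variance components are not given. I set the baseline variance to 1, the ICC to 0.7 (intercept variance 0.7, residual variance 0.3), the slope variance to 0.02 × 0.3 = 0.006 per squared visit interval, and the intercept-slope correlation to 0. Dropout rises linearly to its final value. Tests are two-sided. The treatment test is taken to be the group-by-time term.

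**Step 1: are the stated powers consistent with each other?** Power 0.83 at alpha 0.05 implies a non-centrality of 0.954 + 1.960 = 2.914.
- At alpha 0.025: Φ(2.914 − 2.241) = 0.749 (stated 0.75).
- At 20% attrition: Φ(2.914 × √(0.8/0.7) − 2.241) = 0.809 (stated 0.80).

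They agree.

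**Step 2: reproduce the stated power.** The generalised least squares variance v of the week-12 effect is the relevant diagonal element of (Σ X′V⁻¹X)⁻¹, summed over arms and dropout patterns. Power is Φ(0.5/√v − z). With linear time and a free baseline, v = 0.0290 and 0.5/√v = 2.94. Power is 0.836 at alpha 0.05 and 0.756 at alpha 0.025; at 20% attrition the latter is 0.800. The article states 0.83, 0.75 and 0.80. The assumed values are therefore compatible with the plan, though not the only ones that are.

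**Step 3: remove only the baseline group term, at 30% attrition.**

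| Time coding | Baseline | v | Power, 0.05 | Power, 0.025 |
|---|---|---|---|---|
| Linear | free | 0.0290 | 0.836 | 0.756 |
| Linear | common | 0.0256 | 0.879 | 0.812 |
| Categorical | free | 0.0321 | 0.797 | 0.709 |
| Categorical | common | 0.0287 | 0.840 | 0.761 |

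For linear time the variance ratio is 0.0256/0.0290 = 0.88, a 12% reduction.

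**Step 4: vary the assumptions.** With linear time and an intercept-slope correlation of −0.3, power at alpha 0.025 goes from 0.762 to 0.843. With +0.3 it goes from 0.752 to 0.788.

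A wider grid covered ICC 0.30 to 0.80, slope/residual ratio 0 to 0.15, correlation −0.5 to 0.3, two dropout shapes, and d scaled by the pretest or the posttest SD. In it, 72 parameter sets gave the stated 0.83 within 0.02. Across those sets:
- the variance ratio ran from 0.75 to 1.00, with median 0.89, equivalent to about 120 × 0.89 = 107 participants for the same precision;
- median power at alpha 0.025 rose from 0.75 to 0.80, with a range after the change of 0.73 to 0.87.

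**Step 5: closed-form check.** For complete data at two timepoints with correlation ρ, the change-score variance is proportional to 2(1 − ρ) and the baseline-adjusted variance to 1 − ρ². Their ratio is (1 + ρ)/2: 0.75, 0.80 and 0.85 at ρ = 0.5, 0.6 and 0.7. The direction and order of size agree with the mixed-model results.

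**Step 6: cost under a non-linear effect.** Use linear time, the Step 2 parameters and a true week-12 effect of 0.50.
- Late-emerging effect (10%, 40% and 100% of the final value at weeks 4, 8 and 12): the free-baseline model estimates 0.478, the common-baseline model 0.462.
- Early effect (60%, 85% and 100%): 0.503 and 0.520.

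**The case against.** The strongest reply is that nothing here is an error. Time, group and their interaction form a standard specification that is unbiased under randomisation. The sample size was set for the planned mixed model, and the resulting powers are openly reported. The article is a summary, and baseline handling may be refined in an analysis plan that is not shown. All of this stands, except that the fixed effects are stated in the article, so commenting on them is not a complaint about a missing detail.

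A reader might go further and infer any of the following, none of which the documents support:
- **The planned test is biased or the 0.83 is wrong.** The test is valid, and the stated powers agree with one another and with a free-baseline model.
- **The baseline score is thrown away.** The model uses it, but as part of a change.
- **The change certainly restores 0.80 at the Bonferroni level.** The variance components are undisclosed, and among compatible values the gain can approach nil.
- **A common baseline together with a move to categorical time brings the same benefit.** If the linear model is the planned one, making both changes takes power at alpha 0.025 only from 0.756 to 0.761. The gain belongs to the baseline constraint with time coding held fixed.

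**Conclusion.** The point holds as one of efficiency. As written, the primary model estimates a baseline difference that randomisation sets to zero in expectation, and it pays for this in variance.

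The direction is secure: the constraint did not increase the variance in any parameter set that matched the stated power. The size is less certain, because it depends on assumed variance components, dropout shape, two-sided testing and the SD used for d. The best single description is a variance reduction of about 11 to 12%. With linear time and 30% attrition that is worth about 0.05 of power at alpha 0.025, roughly what the article otherwise obtains only by lowering attrition to 20%. The change is worth making before analysis, but the trial's conclusions would not be invalid without it.

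**What to change.** Keep whatever coding of time is planned, set time zero at baseline, and use fixed effects of time and group-by-time without a group main effect, so that both arms share one baseline mean. With categorical time, this means group terms at weeks 4, 8 and 12 only. Apply it to OASIS, ODSIS and all secondary scales, and state it before the data are analysed.

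A model of weeks 4, 8 and 12 with the baseline score as covariate is a close alternative but not an identical one. It drops participants who have baseline data only, which matters with 30% attrition and an intention-to-treat commitment.

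The cost is one term in the model specification, with no extra participants or measurements. If time is linear, add a sensitivity analysis with categorical time and the same common baseline, because the constrained linear estimate is slightly more sensitive to a non-linear treatment effect.

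### The random-effects structure of the primary models is left to be chosen by fit on the trial's own data, although the sample size assumed a random intercept and slope

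*Protocol article*

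**What the plan says.** Three statements in Data analysis define how the primary model is reached.

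- The random part is open: "intercepts and/or slopes will be allowed to vary on the level of the individual where appropriate".
- The basis for settling it is fit to the trial data. So that nested models can be compared by fit, "models will be estimated via maximum likelihood estimation during model building".
- Only then comes the fit that is reported: "Final models will utilize restricted maximum likelihood estimation".

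The fixed part is not open: "time and treatment group as well as their interaction will be included as fixed effects".

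The Sample size section ties the calculation to the planned linear mixed models and says: "Model parameters (random intercept/slope, residual variance) required for this calculation were estimated from similar data from a previous trial". With "30% research attrition at the primary endpoint" and d = 0.5, "a sample size of 120 (iUP=80, WLC=40) was estimated to yield sufficient statistical power of 0.83". It gives 0.75 at a Bonferroni level of 0.025, and 0.80 at that level with 20% attrition. It does not give the variance values.

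**The concern.** The sample size rests on one structure, and the analysis section allows a simpler one if the data seem to favour it. This is more than detail left for a statistical analysis plan. The protocol states a procedure, and a plan that followed it faithfully would inherit it.

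The structure matters because slope variation between patients is part of the uncertainty in a group-by-time effect. A model without the random slope counts only part of that variation, so its standard error is too small. A fit comparison has limited ability to detect slope variance with 120 patients, four visits and 30% attrition, and failing to detect it is not evidence that it is absent. The error runs in the anti-conservative direction. As the choice is made per model, OASIS and ODSIS could also end up with different structures.

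**Working it through.** **Inputs from the protocol.** 80 v 40 patients; visits at baseline and weeks 4, 8 and 12; attrition 30% (or 20%); d = 0.5; power 0.83, 0.75 and 0.80 as above. A level of 5% is implied by 0.025 for each of two outcomes.

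**Assumed.** Two-sided test, linear time, baseline SD 1, dropout rising linearly and completely at random, intercept and slope uncorrelated. The variances are not given, so pairs are used: intercept share ρ (residual variance 1 − ρ) and variance v of the slope over the whole 12 weeks.

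**Step 1: the plan's own figures.** The step from 0.83 to 0.75 follows directly. Power 0.83 needs 1.960 + 0.954 = 2.914 standard errors, and Φ(2.914 − 2.241) = 0.749. The 0.83 itself cannot be derived from the article alone: for ρ from 0.4 to 0.8 and v from 0 to 0.5, power runs from 0.44 to 0.96. With power = Φ(0.5/SE − z), and SE from the generalised least squares information matrix, four pairs come within 2 points of all three stated figures. For example, ρ = 0.75 and v = 0.15 give SE 0.171, 0.5/0.171 = 2.92 and Φ(2.92 − 1.96) = 0.83.

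**Step 2: why dropping the slope matters.** Take complete data with time coded 0, 1/3, 2/3, 1. The sum of squares about the mean is S = 0.25 + 0.028 + 0.028 + 0.25 = 0.556. The true variance of the 12-week slope difference is (v + (1 − ρ)/S)(1/80 + 1/40). A random-intercept model pools the slope variation into the residual, which has about 3 degrees of freedom per patient, and so reports about (v/3 + (1 − ρ)/S)(1/80 + 1/40). It counts one third of v. True level = 2(1 − Φ(1.96√R)), where R is the ratio of reported to true variance:

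- ρ = 0.70, v = 0.06: R = (0.02 + 0.54)/(0.06 + 0.54) = 0.933; level 5.8%.
- ρ = 0.75, v = 0.15: R = (0.05 + 0.45)/(0.15 + 0.45) = 0.833; level 7.4%.
- ρ = 0.80, v = 0.25: R = (0.083 + 0.36)/(0.25 + 0.36) = 0.727; level 9.5%.
- v = 0: R = 1; level 5%.

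**Step 3: choose by fit, then test.** 4,000 trials per pair were simulated with no treatment effect, 80 v 40 and 30% dropout. The two structures were compared by ML, the chosen one was refitted by REML, and group-by-time was tested at 5% (t, 118 df). Monte Carlo SE is √(0.05 × 0.95/4000) = 0.35 points. The article names no criterion, so AIC and a 5% likelihood-ratio test (LRT, 2 df) were both tried.

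| ρ, v | Power (stated 0.83 / 0.75 / 0.80) | Slope dropped, AIC / LRT | Rejects: slope kept | AIC choice | LRT choice | Intercept only |
|---|---|---|---|---|---|---|
| 0.665, 0 | 0.831 / 0.750 / 0.794 | none to find | 4.4% | 4.6% | 4.7% | 4.7% |
| 0.70, 0.06 | 0.832 / 0.752 / 0.795 | 84% / 93% | 4.5% | 5.1% | 5.3% | 5.5% |
| 0.75, 0.15 | 0.832 / 0.752 / 0.796 | 50% / 67% | 4.9% | 5.6% | 6.0% | 7.0% |
| 0.80, 0.25 | 0.829 / 0.748 / 0.790 | 11% / 21% | 4.8% | 5.2% | 5.5% | 9.1% |

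A separate simulation at three pairs that also reproduce 0.83 gave 4.6 to 5.7% with the slope kept, 5.0 to 6.3% with AIC, 5.1 to 6.9% with the LRT and 5.1 to 9.6% with an intercept only. Direction and order of size agree. The intercept-only column also agrees with Step 2.

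**The case against.** The strongest case against is that the effect is small and cannot be established from the documents. This largely stands. The variances come from a previous trial that is not shown, and the slope variance there may have been close to zero, in which case nothing is lost. The selection criterion is an assumption too. Several results after selection cannot be told apart from 5%. Larger figures can be produced, but some need variances that conflict with the protocol's own power. For example, ρ = 0.60 with v = 0.30 implies power of about 0.62, not 0.83. The trial also calls itself exploratory, which lowers the stakes.

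A reader might go further in three ways, none of which the documents support.

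- That the week-12 treatment contrast is left unfixed by this procedure. Choosing random effects alters the standard error, not which contrast is tested, and time, group and their interaction are always included. How time is coded and which contrast is named can be left to a statistical analysis plan.
- That the fixed effects are also selected by fit. The ML comparison could technically cover them, but the text does not say so.
- That the 5% test is seriously broken. Rejection rates counted only in trials where the slope was dropped look worse, but they are not the error rate of the whole procedure.

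What remains is that the article commits to choosing by fit and gives no rule, when it already had a structure in hand from the sample size calculation.

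**Conclusion.** The point holds and is minor. The structure for the primary test is chosen from the outcome data, and it may be simpler than the one behind the sample size. Where true slope variance exists, selection by fit raises the error rate by up to about 1 percentage point in each simulation, to an overall range of about 5 to 7%. A random intercept only, which the wording also permits, can reach about 9 to 10%. Keeping the slope holds the rate at about 5%. With no true slope variance there is no inflation.

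These sizes rest on assumed variances calibrated to the stated power, linear time, dropout completely at random, two assumed selection rules and a 5% level that the article only implies.

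**What to change.** In Data analysis, replace the open wording on random effects with a fixed statement for both primary outcomes: the OASIS and ODSIS models will each include a random intercept and a random slope for time, as assumed in the sample size calculation, fitted by REML. Add a fallback set in advance and used only if the model does not converge, for example setting the intercept-slope covariance to zero as the first step. Keep fit-based comparison of structures for sensitivity analyses.

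A fuller respecification, such as categorical time with unstructured covariance, is a legitimate alternative but is not needed to cure this defect.

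The cost is a change of wording. If slope variance is negligible, standard errors will be slightly wider than necessary: in the simulated case with none, the test rejected 4.4% of the time instead of 4.7%, a difference within simulation error. The sample size need not change, because it was already based on random intercept and slope parameters.

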### Data management

All potential participants for the project will be given a referral code. Participants who proceed from assessment to the trial will be given a trial code. The pre-therapy assessment interview including a shortened version of the M.I.N.I. will take place over the phone. All other screening and assessment information will be gathered via the Qualtrics platform. Data will be collected in a pseudo-anonymized way (not immediately identifiable when looking at the data set but by using codes the data may be linked back to the individual if required); however, once all data is collected, it will be transferred to a database via Qualtrics and completely anonymized for each participant.

All regulations set by the ethics committees as well as data protection recommendation offered by the Data Protection Impact Assessment will be observed. The integrity of the main analyses will be secured by parallel datasets with regularly updated versions with one of them being in anonymized form. Data management procedures will be shared with the Trial Management Group and Trial Steering Committee (see below).

### Governance and oversight of the trial

The Trial Management Group (TMG) will be established to oversee day-to-day operations of running the trial such as training of supporters, recruitment of participants, clinical governance and ethical issues, adverse events and data management processes. The TMG will meet quarterly or as needed. It will consist of the principal investigator (PI), co-principal investigator, trial managers and service representatives. The TGM will regularly discuss any potential changes to the trial protocol that will then be brought to the Trial Steering Committee (TSC). The TSC will consist of the abovementioned members of the TMG, an independent academic, a public health service manager responsible for the services in the area and a service user representative. The TSC will meet every 6 months over the course of the project and will have the function of overseeing the project. The PI will report to the committee on progress regarding the trial and seek perspectives from the TSC regarding any issues arising.

## Discussion

This project aims to make contributions to the existing state of the art of our knowledge about the efficacy of the Unified Protocol (UP) in its varied forms of delivery ( [24]). This is the first study to analyse the effectiveness of an online version of the UP (iUP) in primary care in an English-speaking country. It will also be the first online version of the UP tested that is being developed in collaboration with the original developers of the UP and a leading digital mental health care company with over 15 years of experience in delivering digital mental health interventions.

The UP has already shown efficacy/effectiveness in a number of trials when delivered in a face-to-face format. However, how the UP performs in an online format has yet to be examined. Online treatments have important differences with face-to-face treatments (for instance, with regard to dissemination, implementation and access to evidence-based treatments). Therefore, the findings obtained with this study could represent a very significant contribution to the literature about the UP and an Internet-delivered transdiagnostic treatment for anxiety and depression in an ecological setting in Ireland. The potential of iUP, specifically in the context of a primary care psychology service, is in its use in a stepped-care model, where iUP may show its usefulness as a low-intensity intervention suitable particularly for clients that would otherwise be on the wait-list (although the wait-list in the service where the study is going to be conducted offers some resources, it is envisaged that iUP will be superior to those resources).

Furthermore, there is literature showing that the UP leads to similar results than disorder-specific CBT [21, 22]. However, transdiagnostic treatments such as the UP offer important practical advantages compared to disorder-specific treatments, such as a better management of comorbidity. In this sense, this study would provide valuable data in a context where mental health care resources are limited. Finally, this project aligns with the e-health strategy for Ireland proposed by the Irish public health service provider, the Health Service Executive (HSE) aimed to integrate technology enabled solutions within Irish healthcare. It seeks to improve service efficiency in primary care within the HSE by providing an evidence-based solution for addressing depression, anxiety and related disorders.

If positive, the intervention tested in this project could help to increase access to empirically supported treatments, thereby reducing waiting lists to receive adequate treatment. In this way, the project will build on recent work that has deployed the SilverCloud disorder-specific interventions for anxiety and depression as part of the health services mental health care offering. While not directly studied in this project, it is likely that an intervention such as iUP, offered to people that would otherwise be on the wait-list and integrated in a stepped-care model would also show economic benefits as some studies examining similar interventions have already shown [54]. The iUP can become an important part of (public) mental health provision and can further supplement other forms of care. It can help to address the societal need for a timely and accessible provision of mental health support. Given that UP is also an intervention that is well-established in other formats such as face-to-face individual/group therapy, the availability of an internet-based version can potentially add to the layered (stepped-care) overall mental health approach, where the clients and clinician may be familiar with important intervention concepts at several levels of provision (low-intensity vs. high-intensity).

